## PART 1: APPLICATION FORM

### GENERAL INFORMATION ABOUT THE PROPOSED RESEARCH STUDY

**1. Study Title (Max. 255 characters including spaces)**

Characterisation of multimorbidity clusters and trajectories using data-driven approaches in a nationally-representative population

**2. Research Area** (place 'X' in all boxes that apply)

|                          |   |                      |   |
|--------------------------|---|----------------------|---|
| Drug Safety              |   | Economics            |   |
| Drug Utilisation         | X | Pharmacoeconomics    |   |
| Drug Effectiveness       |   | Pharmacoepidemiology |   |
| Disease Epidemiology     | X | Methodological       | X |
| Health Services Delivery | X |                      |   |

**3. Does this protocol describe an observational study using purely CPRD data?**

|     |   |    |  |
|-----|---|----|--|
| Yes | X | No |  |
|-----|---|----|--|

**4. Does this protocol involve requesting any additional information from GPs, or contact with patients?**

|     |  |    |   |
|-----|--|----|---|
| Yes |  | No | X |
|-----|--|----|---|

If yes, provide the reference number:

### 10. Institution conducting the research

[figure not shown]

# Medicines & Healthcare products Regulatory Agency

[figure not shown]

|                           |     |  |    |  |
|---------------------------|-----|--|----|--|
| Same as Sponsor?          | Yes |  | No |  |
| Institution/Organisation: |     |  |    |  |
| Address:                  |     |  |    |  |

## 11. Data Access Arrangements

Indicate with an 'X' the method that will be used to access the data for this study:

|                                  |  |   |
|----------------------------------|--|---|
| Study-specific Dataset Agreement |  | X |
|----------------------------------|--|---|

Institutional Multi-study Licence

|                     |  |
|---------------------|--|
|                     |  |
| Institution Name    |  |
| Institution Address |  |

Will the dataset be extracted by CPRD?

|     |   |    |  |  |
|-----|---|----|--|--|
| Yes | X | No |  |  |
|-----|---|----|--|--|

If yes, provide the reference number: 00070707

## 12. Data Processor(s):

|                                    |                                           |  |
|------------------------------------|-------------------------------------------|--|
| Processing                         | X                                         |  |
| Accessing                          | X                                         |  |
| Storing                            | X                                         |  |
| Processing area (UK/EEA/Worldwide) | UK                                        |  |
| Organisation name                  | Queen Mary University of London           |  |
| Organisation address               | [name] |  |

[figure not shown]

|                                    |                                           |  |
|------------------------------------|-------------------------------------------|--|
| Processing                         |                                           |  |
| Accessing                          |                                           |  |
| Storing                            |                                           |  |
| Processing area (UK/EEA/Worldwide) |                                           |  |
| Organisation name                  | Queen Mary University of London           |  |
| Organisation address               | [name] |  |

[Add more processors as necessary by copy and pasting a new table for each processor]

## INFORMATION ON DATA

### 13. Primary care data (place 'X' in all boxes that apply)

|           |   |            |   |
|-----------|---|------------|---|
| CPRD GOLD | X | CPRD Aurum | X |
|-----------|---|------------|---|

Reference number (if applicable): 00068753

### 14. Please select any linked data or data products being requested

#### Patient Level Data (place 'X' in all boxes that apply)

|                                               |   |                                                          |  |
|-----------------------------------------------|---|----------------------------------------------------------|--|
| ONS Death Registration Data                   | X |                                                          |  |
| HES Admitted Patient Care                     | X |                                                          |  |
| HES Outpatient                                |   |                                                          |  |
| HES Accident and Emergency                    |   | NCRAS Cancer Registration Data                           |  |
| HES Diagnostic Imaging Dataset                |   | NCRAS Cancer Patient Experience Survey (CPES) data       |  |
| HES PROMS (Patient Reported Outcomes Measure) |   | NCRAS Systemic Anti-Cancer Treatment (SACT) data         |  |
| CPRD Mother Baby Link                         |   | NCRAS National Radiotherapy Dataset (RTDS) data          |  |
| Pregnancy Register                            | X | NCRAS Quality of Life Cancer Survivors Pilot (QOLP)      |  |
| Mental Health Data Set (MHDS)                 |   | NCRAS Quality of Life Colorectal Cancer Survivors (QOLC) |  |

#### Area Level Data (place 'X' in one Practice / Patient level box that may apply)

| Practice level (UK)                                                             |   | Patient level (England only)                        |   |
|---------------------------------------------------------------------------------|---|-----------------------------------------------------|---|
| Practice Level Index of Multiple Deprivation                                    | X | Patient Level Index of Multiple Deprivation         | X |
| Practice Level Index of Multiple Deprivation (index other than the most recent) |   | Patient Level Index of Multiple Deprivation Domains |   |
| Practice Level Index of Multiple Deprivation Domains                            |   | Patient Level Carstairs Index for 2011 Census       |   |

[figure not shown]

|                                                                             |  |                                               |  |
|-----------------------------------------------------------------------------|--|-----------------------------------------------|--|
| Practice Level Carstairs Index for 2011 Census (Excluding Northern Ireland) |  | Patient Level Townsend Score                  |  |
| 2011 Rural-Urban Classification at LSOA level                               |  | 2011 Rural-Urban Classification at LSOA level |  |

Reference / Protocol number (where applicable):

**15. Are you requesting linkage to a dataset not listed above?**

|     |                          |    |                                     |
|-----|--------------------------|----|-------------------------------------|
| Yes |  | No |  |
|-----|--------------------------|----|-------------------------------------|

If yes, provide the Non-Standard Linkage reference number:

**16. Does any person named in this application already have access to any of these data in a patient identifiable form, or associated with an identifiable patient index?**

|     |                          |    |                                     |
|-----|--------------------------|----|-------------------------------------|
| Yes |  | No |  |
|-----|--------------------------|----|-------------------------------------|

If yes, provide further details:

[figure not shown]

## PART 2: PROTOCOL INFORMATION

### Applicants must complete all sections

#### A. Lay Summary (Max. 250 words)

Multimorbidity describes the situation where an individual is affected by 2 or more health conditions. Studies have shown that multimorbidity is becoming more common, and the National Health Service does not currently have services designed to tackle it well. People living with multimorbidity often need to take multiple medications and require regular contact with health services. Recent research has shown that multimorbidity exists in 'clusters', with groups of common conditions (e.g. type 2 diabetes, chronic pain, and depression) often co-existing.

Using the health records of several million people held by CPRD, we will explore unanswered questions relating to multimorbidity. Our research will focus on using novel statistical and computer science techniques to look for clusters and patterns in this health record data. We will examine these clusters and patterns of multimorbidity to better understand how they affect particular people (e.g. people prescribed specific or multiple medications, or people living with specific conditions such as cancers and human immunodeficiency virus (HIV)) and populations (e.g. people from different ethnic groups). Our approach, in combination with using historic data available from CPRD, will also allow us to uncover how and why multimorbidity develops over time, and if it is associated with early death.

We expect that the impact of our research will be wide-ranging, including supporting improvements in health and social care for multimorbidity and perhaps more efficient use of limited NHS funds.

#### B. Technical Summary (Max. 300 words)

Our proposal seeks to deliver new knowledge on multimorbidity through the application of hypothesis-generating, data-driven analytical tools to a large-scale electronic health record dataset from a nationally-representative population. We seek to expand on previous multimorbidity research (which focuses predominantly on 30-40 common chronic conditions) to define clusters and trajectories of multimorbidity across ~200 long-term conditions. This large set of conditions have been defined through a rigorous consensus-building process and extensive review of existing validated code sets (including previously-published CPRD studies undertaken by CALIBER and the Cambridge Multimorbidity group (1–3)).

We will initiate our analyses using a cross-sectional design, applying data-driven clustering (unsupervised machine learning) to identify clusters of multimorbidity in England population across our extensively-curated ~ 200 long-term conditions obtained from primary care data and linked Hospital Episode Statistics (HES). We will stratify our analysis by ethnicity to identify how multimorbidity clusters across ethnic groups (including White, Black African and Caribbean, and south Asian).

Subsequent to this hypothesis-generating clustering, we will use an observational cohort design to investigate how multimorbidity clusters develop from index conditions and how they change over time, including to death (using linked Office for National Statistics mortality data). At this point, we will focus on a limited number of multimorbidity clusters (up to 8) selected to ensure we generate new knowledge, e.g. clusters which include less-studied conditions such as cancer or human immunodeficiency virus, as well as those where there is variation by ethnicity. We will then use epidemiological analyses, including Cox model, adjusted by socioeconomic characteristics (age, sex, ethnicity, Index of Multiple Deprivation), and time-dependent variables (e.g. risk factors, clinical measurements) to characterise these trajectories. Additionally, we will apply artificial intelligence techniques (including supervised and unsupervised machine learning) for focused analyses to examine the interrelationship between specific multimorbidity clusters under study and prescribing/polypharmacy patterns.

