#### J. Planned use of linked data (if applicable):

This study will use individual level anonymised data within linked primary and secondary care records. The use of linked data from the NHS Hospital Episode Statistics (HES) for admitted-patient care will allow us to identify hospital-

[figure not shown]

coded conditions that contribute to multimorbidity, to characterise pregnancies, and to add information on health service utilisation, such as number of hospital admissions per year, and to obtain a higher completeness of ethnicity data (a core variable to our study). Moreover, the use of HES data will enable us to undertake validation of diagnosis across primary and secondary care (e.g. HIV and cancer). The linkage to the Office for National Statistics Death registries will allow us to know the cause of death and therefore understand the most common cause of death according to the patterns of diseases' clusters.

Linked area-based measures of deprivation will include the Indices of Multiple Deprivation (IMD) for both patient and practice level. The IMD is an estimate of socioeconomic status that play an important role to multimorbidity. We will use patient level IMD where available. For patients without linked patient level IMD, we will use practice level IMD as a proxy.

We expect that the identification of specific multimorbidity clusters and their different trajectories across ethnic groups will help identify groups of patients who may share similar prognosis and health care needs. Our study findings will support clinicians in the stratification of clinical care and will contribute to preventive strategies across multimorbid conditions. We expect that our study outputs may help improve patient care either directly, e.g. by recognising a common cluster of multimorbidity linked to a specific disease, or indirectly providing scientific support to the inclusion of multimorbidity in clinical practice guidelines and public health policies.

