#### M. Exposures, Outcomes and Covariates

##### Research Aim A)

This analysis does not have a specific exposure since it is a descriptive analysis of clusters of multimorbidity. Nevertheless, the clusters will be closely investigated according to covariables such as sex, age group, ethnicity (White, Black African and Caribbean, and south Asian) and socioeconomic deprivation levels (using the Index of Multiple Deprivation). The outcome of this analysis are the clusters of multimorbidity, defined using a list of 220 conditions (Appendix 1).

[figure not shown]

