### P. Plans for addressing missing data

We will assume that the individuals who do not have any recorded code do not have the disease (for further discussion, please also see Section T. Limitations on the study design). We will include patients who have complete data for the stratification variables (e.g. sex, age and ethnic groups) and who have linked measures of deprivation. Given the high levels of missingness for some covariates, i.e. body mass index, total cholesterol, and alcohol intake specific statistical techniques will be applied to handle missing-not-at-random data, e.g. sensitivity analysis and multiple imputation techniques where appropriate.

The design of the study assumes that patients who do not meet the criteria according to the coding algorithm do not have the disease. This may introduce biases due to under-reporting or misreporting. Please see section O for further details.

In the main analyses, where patients will be stratified by age and sex, any individuals with missing data for either will be excluded. In addition, patients without data for ethnicity and deprivation will be excluded from sensitivity analyses.

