## T. Limitations of the study design, data sources, and analytic methods

There are a few limitations to our study design, analytic methods and use of data sources:

- Adding only 'acceptable patients' could potentially introduce a selection bias to our study. Acceptable patients might underrepresent a group of patients that are difficult to engage, e.g. those who may often change GP practice but who are also multimorbid, and who might be from minority ethnic groups. Similarly, including only 'up to standard' data will assure high quality data, but could introduce selection bias by including general practices with better quality of, and access to, healthcare and access to primary healthcare. However, including only 'up to standard' data from acceptable patients will ensure high quality data, an essential aspect to work both with longitudinal analysis. This limitation will be addressed in our study discussion.
- The cluster analysis is dependent on the measures (e.g. variables/conditions) used to characterise the objects (e.g. individuals). Despite our comprehensive list of conditions (we will expand on the existing ~40 conditions commonly used in most of the UK's multimorbidity studies due to its data quality (mostly incentivised via QOF) to include a larger set of clinically-relevant conditions (n = 220)) our clustering solution might not be generalised as it is dependent upon the included conditions (e.g. the addition or exclusion of variables/conditions influences the clustering solution we get from the analysis). However, it will cover a broader set of conditions, compared to various studies on multimorbidity. We are aware that recording of non-incentivised conditions will be less comprehensive and therefore this may introduce bias from coding frequency/accuracy.
- We have included a few sexually transmitted conditions in our study (e.g. HIV, chronic hepatitis) that might be under-reported in the CPRD linked dataset for reasons of confidentiality, also given that in the UK, most consultations involving sexually transmitted infections are diagnosed and treated at sexual health service centres (2).
- Our study might be subject to misclassification due to unrecorded, miscoded and undiagnosed diseases. Likewise, a patient with no disease diagnoses record will be considered as disease free, even though the lack

[figure not shown]

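### Aim A pools primary-care and admitted-patient codes and treats no code as no disease, which can inflate co-occurrence between unrelated conditions that are poorly recorded

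*Protocol*

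**What the plan says.** Section B (Technical Summary) says that Aim A will cluster roughly 200 "long-term conditions obtained from primary care data and linked Hospital Episode Statistics (HES". In the linked-data request (item 14), Admitted Patient Care is the only HES product ticked; Outpatient and Accident and Emergency are not. Section J confirms the role of this source: "The use of linked data from the NHS Hospital Episode Statistics (HES) for admitted-patient care will allow us to identify hospital", continuing after a page break, "coded conditions that contribute to multimorbidity".

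Section P gives the rule for everything else: "We will assume that the individuals who do not have any recorded code do not have the disease".

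The protocol nowhere writes an either-source rule in those words, but these statements together amount to one: a condition is present if either source has a code, and absent otherwise.

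Section T concedes that recording is uneven: "We are aware that recording of non-incentivised conditions will be less comprehensive and therefore this may introduce bias from coding frequency/accuracy".

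For Aim A, section M says that "the clusters will be closely investigated according to covariables such as sex, age group, ethnicity" and deprivation. Section O stratifies by sex, age group and ethnic group. Hospital admissions appear in section M as a secondary exposure for Aims B and C. In section N, health care utilisation enters under Aim B, after the clusters have been formed.

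**The concern.** The clusters are primary outcome (a), so the rule that decides who has which condition shapes the main result. Under the either-source rule, an admitted person has two chances of having a condition recorded and a person never admitted has one. If primary care records a condition nearly completely, the second chance adds little. If it does not, admitted people carry more recorded conditions than others with the same true disease, and pairs of such conditions occur together more often than their separate prevalences imply.

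The conditions most exposed are the non-incentivised ones that this study adds to the usual list of about 40. Sections B and N then choose up to 8 clusters for Aim B partly because they contain less-studied conditions or vary by ethnicity, and that choice leans towards the same conditions. The Aurum replication is to use the same methods and population specifications, so agreement between GOLD and Aurum would not test for this artefact. At stake is whether a cluster described as new reflects disease or where the diagnosis was coded.

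**Working it through.** **The plan's own figures.** The protocol gives no figure for recording completeness, admission share or codes per admission. Its one calculated sample size, 1.96² × 0.272 × 0.728 / 0.002² = 190,174.6, reproduces the stated 190,174, but it concerns the precision of a prevalence and does not bear on this point.

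**Inputs, all assumed.** Let q be the share ever admitted, s the probability that a true condition is coded in primary care, and h the probability that it is coded in HES if the person was admitted. Take two conditions that are truly independent, with admission unrelated to either.

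**Formula.**
- Capture if admitted: a = 1 − (1 − s)(1 − h)
- Average capture: m = q·a + (1 − q)·s
- Observed/expected co-occurrence: O/E = [q·a² + (1 − q)·s²] / m², which equals 1 + q(1 − q)(a − s)² / m²

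The second form shows that O/E exceeds 1 whenever some but not all people are admitted and HES adds anything (a > s).

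**Worked case**, q = 0.3, s = 0.2, h = 0.7: a = 1 − 0.8 × 0.3 = 0.76; m = 0.3 × 0.76 + 0.7 × 0.2 = 0.368; O/E = (0.3 × 0.5776 + 0.7 × 0.04) / 0.1354 = 0.2013 / 0.1354 = 1.49.

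**Range at q = 0.3:**

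| Primary-care capture s | h = 0.3 | h = 0.5 | h = 0.7 | h = 0.9 |
|---|---|---|---|---|
| 0.2 | 1.16 | 1.33 | 1.49 | 1.63 |
| 0.4 | 1.03 | 1.08 | 1.13 | 1.19 |
| 0.8 | 1.001 | 1.003 | 1.006 | 1.009 |

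The admitted share matters less than s: with s = 0.3 and h = 0.8, O/E stays between 1.22 and 1.30 for q from 0.1 to 0.5.

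**Does it form clusters?** A simulation used the planned GOLD size of 3 million, 60 wholly independent conditions (30 weakly and 30 well coded), an assumed true prevalence of 3% and 30% admitted. Ward clustering on 1/(O/E) was cut at two clusters.
- Recording probability for weakly coded conditions 0.3 without and 0.7 with admission, or 0.1 and 0.6: mean O/E between them 1.19 or 1.84, and all 30 fell in one cluster with the other 30 in the second.
- 0.5 and 0.8: mean O/E 1.06, with one condition misplaced on each side.
- 0.7 and 0.9: mean O/E 1.01, no separation.
- HES removed: O/E 1.00, no separation.

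A smaller run (400,000 people, 0.3 and 0.7, average linkage) had mean O/E of 1.20 but did not separate the two groups. Excess co-occurrence is therefore certain under the assumptions; cluster formation depends on method and sample size, and neither run contained real disease associations to compete with it.

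**Would splitting by admission be a clean test?** Within each admission stratum the smaller run gave O/E of 1.00, but only because admission was simulated as unrelated to disease. Suppose two independent conditions at 5% prevalence, with admission probability 25%, 50% and 67% for none, one and both.
- P(admitted) = 0.9025 × 0.25 + 0.095 × 0.50 + 0.0025 × 0.67 = 0.2748
- P(both | admitted) = 0.001675 / 0.2748 = 0.0061
- P(one given condition | admitted) = (0.0475 × 0.50 + 0.001675) / 0.2748 = 0.0925
- O/E = 0.0061 / 0.0925² = 0.71

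The split therefore creates a bias of its own, in the opposite direction.

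**The case against.** Pooling the two sources is a reasoned choice, not a mistake. Section J gives its purposes, including cross-source validation of diagnoses such as HIV and cancer. The study is declared hypothesis-generating. Section T already admits weaker recording of non-incentivised conditions, misclassification, and dependence of the clusters on the conditions included. Section N allows low-prevalence conditions to be revised if reporting bias is a worry. A sensitivity analysis by source may sit in an analysis plan not shown here.

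Much of this stands. The protocol is not in contradiction with itself, and a repeat run already planned elsewhere would answer most of the point. What remains is that the protocol itself fixes the source rule and the no-code rule, and none of its safeguards reaches the mechanism. Section T speaks of under-recording, not of recording that depends on admission. Validating a diagnosis does not undo admission-dependent detection of pairs. A prevalence cut-off removes rare conditions, not weakly recorded ones. Stratifying by age removes only the age-related part of admission.

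A reader might go further and infer that unrelated conditions will cluster, or that novel clusters and ethnic differences will be artefacts. The documents do not support that. Describing recording as less comprehensive does not establish capture of 20-30%; that one admission reveals several conditions is an inference; and an ethnic difference would arise this way only if admission or capture differed between groups, which the protocol does not state. Nor is HES the only route: uneven consultation can produce the same bias within primary-care data.

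**Conclusion.** The point holds as a limited one. The either-source rule, with no code taken as no disease and HES restricted to admitted care, can inflate co-occurrence between unrelated conditions that primary care records poorly, and nothing stated for Aim A would reveal it. Under assumed values (30% admitted, HES capture 30-90%, admission independent of disease), the inflation is about 1.2-1.6 at 20% primary-care capture, 1.03-1.2 at 40% and about 1.01 or less at 80%. It is negligible for well-recorded conditions. Whether it would form a cluster among real associations is open. This calls for a check by source and a caveat; it is not a reason to drop HES or to discard clusters.

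**What to change.** Keep the pooled sources as the main derivation. In section N (Aim A), add that the clusters will be derived again from primary-care codes only, in GOLD and in the Aurum replication, and state before the results are seen how a cluster in one derivation will be matched to one in the other. Since section N assigns each condition to the cluster where its membership is highest, a minimum overlap between assigned condition sets would serve.

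Report clusters, and ethnic differences in clusters, that do not reappear as dependent on hospital ascertainment, and do not call them novel without that caveat. Do not bar them from Aim B: section T says HIV may be under-reported, and a bar would work against the HIV and cancer clusters that Aim B seeks. Do not use an ever/never-admitted split as the test, because admission is itself a consequence of disease.

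Add to section T that recording depends on admission and on contact with care, and that this can create co-occurrence.

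The cost is one extra clustering run per population (overall, each ethnic group, and Aurum) on data already requested. The primary-care-only run will under-capture conditions coded mainly in hospital and is not itself free of contact-driven bias, so a failure to reappear is a flag, not proof of an artefact.
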